## Analyses

### Quantitative analyses

As the study is a feasibility study, we will not be carrying out hypothesis testing to determine if the intervention is effective. Data analysis will follow an intention-to-treat (ITT) protocol and will be used to inform power calculations for a definitive trial in addition to other published sources.

We will calculate and present in a CONSORT flow chart: the number of CYP approached to participate, the number consenting to participate in the study, the number completing the baseline assessment and subsequently allocated to each trial arm, the number of therapy sessions attended by CYP receiving the MCT intervention and the proportion completing the treatment (defined as attending a minimum of four out of eight sessions), and the number completing each of the follow-up assessments in each trial arm. Reasons for drop-out will be recorded where possible and used to help determine the acceptability of the MCT intervention, along with the attrition rates themselves. We will also assess rates of missing data on individual questionnaires (and which elements in particular) and whether any display floor and/or ceiling effects. The acceptability of minimisation will be informed by examining how balanced treatment allocation is across the four factors on which participants are allocated.

We will summarise, as appropriate (e.g. mean/standard deviation; median/inter-quartile range; proportion/95% confidence interval; data range) data for all potential ‘clinical’ outcome measures, overall and by group. The SD of the (potential) primary outcome for a full trial (RCADS-25), along with the estimated attrition rate, will be used to help inform the sample size calculation for the definitive RCT. As MCT is undertaken as groups, we will attempt to estimate the intra-group correlation coefficient in the RCADS-25, as this may also be used to inform the calculation if appropriate. We will also report confidence intervals for the trial arm coefficient from appropriate regression analyses by way of investigating the ‘promise’ of the intervention. A Statistical Analysis Plan will be produced by the study statistician prior to the examination of outcome data.

### Qualitative analyses

All qualitative interviews will be transcribed verbatim. Analysis will be conducted blind to trial outcomes to avoid biased interpretation of findings. Framework analysis [39] will be used, allowing for both inductive and deductive coding. Deductive coding will be informed by Normalisation Process Theory (NPT) [40].

### Economic analyses

Exploratory analysis will be conducted to inform an economic evaluation integrated within a definitive trial, including an analysis of the range of health and social care services used and associated costs; the ability of the quality-adjusted life-year (QALY) to discriminate between groups based on changes in clinical outcomes; and factors likely to influence the incremental cost per QALY. Two generic preference-based measures are being collected to inform health benefit: the CHU-9D and the EQ-5D-Y. Data will be compared to assess whether one measure is more feasible and preferred for a larger scale trial (e.g. through a comparison of missingness). The CHU-9D will be the primary measure as UK preference weights are available [33]. The impact of the EQ-5D-Y will be tested in a sensitivity analysis. Costs will be estimated from the SUQ data collected, using national unit costs [41, 42]. If the data are sufficient, preliminary cost-effectiveness will be conducted, with a time horizon of 6 months.

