## Methods

### Design

Youth Metacognitive Therapy (YoMeta) is a single-blind, randomised feasibility study with 20 weeks, 32 weeks, and 44 weeks of follow-up, comparing group-based MCT (intervention) versus usual treatment (control). Qualitative evaluations will be embedded within the trial. Preliminary economic data will be obtained to inform the optimum way of evaluating cost-effectiveness. Figure 1 shows an overview of the trial design according to CONSORT guidelines [20, 21]. The recommendations for the Interventional Trials 2013 (SPIRIT) Checklist [22, 23] are included in Additional file 1. Figure 2 outlines the schedule of recruitment, interventions, and assessment.

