## Data collection

There will be four assessment time points: baseline, 20 weeks post-randomisation, 32 weeks post-randomisation, and 44 weeks post-randomisation (see Figs. 1 and 2). In order to aid the return of follow-up measures, participants will be offered a range of options for completing measures including returning via post, telephone, or face-to-face (at NHS sites or participants’ home). Participants’ time involvement in the study is 44 weeks. Participants will be offered compensation for completing assessments; each time an assessment is completed and returned, they will be reimbursed with a £10 shopping voucher.

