### Health and Social Care Service-Use Questionnaire (SUQ)

The SUQ will include questions about whether the child has used any primary, secondary, or community-based health and social care and how often they used the service in the last 16 weeks (baseline study visit) or since the last assessment (follow-up study visits). The SUQ will be developed from existing child-relevant SUQs held by the co-applicants and through discussion with the PPI representative, parent advisory group, and clinical members of the study team. Parents/primary caregivers will complete this.

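### The 6-month cost-effectiveness horizon falls between the 20- and 32-week assessments, so costs up to it can be obtained only by splitting a 12-week total by assumption (minor)

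*Protocol article*

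**What the plan says.** Three parts of the protocol article bear on this.

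- **Horizon.** Economic analyses makes the cost-effectiveness work conditional ("If the data are sufficient, preliminary cost-effectiveness will be conducted") and sets its horizon at 6 months ("preliminary cost-effectiveness will be conducted, with a time horizon of 6 months").
- **Schedule.** Data collection states: "There will be four assessment time points: baseline, 20 weeks post-randomisation, 32 weeks post-randomisation, and 44 weeks post-randomisation". Design gives the same follow-up weeks ("randomised feasibility study with 20 weeks, 32 weeks, and 44 weeks of follow-up"), and Data collection adds that "Participants’ time involvement in the study is 44 weeks".
- **Inputs.** For costs, Economic analyses says "Costs will be estimated from the SUQ data collected, using national unit costs". The section on the Service-Use Questionnaire (SUQ) gives its recall period as "in the last 16 weeks (baseline study visit) or since the last assessment (follow-up study visits". For QALYs, "The CHU-9D will be the primary measure as UK preference weights are available", with the EQ-5D-Y in a sensitivity analysis.

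The article gives no reason for choosing 6 months and does not tie it to a visit.

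**The concern.** A within-trial horizon normally ends where costs and utilities are observed. Here it ends about six weeks after one assessment and six weeks before the next.

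The difficulty is mainly with costs. A form that reports use since the last visit yields a total for the whole interval. Nothing in the recall period described says how much of that use fell before week 26. Therapy comes in finite courses (eight weekly group sessions in one arm, normally up to 12 sessions in the other), so use need not be even over weeks 20 to 32, and the pattern need not be the same in both arms. If it differs, the incremental cost is distorted by the splitting rule and not only by sampling error.

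The horizon also leaves out any economic data from the last visit. The stated purpose of this work is to inform an economic evaluation within a definitive trial, and whether costs and utilities still differ after treatment has ended is relevant to that purpose.

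This is an element that the article fixes and that does not fit its own schedule. It is not a detail left to an analysis plan.

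**Working it through.** **Inputs.** Horizon 6 months (Economic analyses). Assessments at 0, 20, 32 and 44 weeks (Design; Data collection). SUQ recall at follow-up is since the last assessment (SUQ section). Assumption: CHU-9D, EQ-5D-Y and SUQ are taken at all three follow-ups. The SUQ section speaks of follow-up visits in the plural, but the schedule figure is not shown.

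**1. Does 6 months coincide with a visit?** Weeks per month = 365.25 / 12 / 7 = 4.348, so 6 months = 26.09 weeks, taken as 26. Distances: 26 − 20 = 6 and 32 − 26 = 6. Other readings do not help. With 4-week months the horizon is week 24, and six months counted from the 20-week visit is week 20 + 26 = 46. Neither is a visit.

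**2. Costs.** Let C1 be a participant's cost from the 20-week SUQ (weeks 0–20), C2 the cost from the 32-week SUQ (weeks 20–32), and f the share of C2 incurred by week 26. Then

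cost to week 26 = C1 + f × C2.

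C1 and C2 are observed; f is not. An even spread gives f = 6/12 = 0.5, while f can lie anywhere from 0 to 1. The even split can therefore misstate a participant's cost by up to half of C2 in either direction. If f averages f_M in the group-MCT arm and f_T under usual treatment, and C2 averages M and T, the even split shifts the incremental cost (taking f as unrelated to the size of C2 within an arm) by

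(0.5 − f_M) × M − (0.5 − f_T) × T.

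This is zero only if the two terms happen to cancel or f is 0.5 in both arms. The article gives no cost figures, so the shift cannot be expressed in money. One illustration of how f could depart from 0.5: eight weekly sessions starting at week s end at week s + 7, so a group starting after week 13 would still be running after week 20, with its remaining sessions early in the 20–32 week interval. The article does not say how often this would happen.

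**3. QALYs.** Trapezoidal area under the curve, cut at week 26, with u0, u20 and u32 the utilities at those weeks:

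- Weeks 0–20: 20 × (u0 + u20)/2 = 10 u0 + 10 u20.
- Interpolated u26 = 0.5 u20 + 0.5 u32.
- Weeks 20–26: 6 × (u20 + u26)/2 = 4.5 u20 + 1.5 u32.
- Total: 10 u0 + 14.5 u20 + 1.5 u32, with weights summing to 26.

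**4. Weights by horizon**

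| Horizon | Months | Baseline | Week 20 | Week 32 | Week 44 | Can SUQ totals be summed whole? |
|---|---|---|---|---|---|---|
| 20 weeks | 4.6 | 50.0% | 50.0% | 0 | 0 | Yes |
| 26 weeks (as stated) | 6 | 38.5% | 55.8% | 5.8% | 0 | No |
| 32 weeks | 7.4 | 31.2% | 50.0% | 18.8% | 0 | Yes |
| 44 weeks | 10.1 | 22.7% | 36.4% | 27.3% | 13.6% | Yes |

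At the stated horizon the 32-week data are used in part, and the 44-week data have zero weight in both costs and QALYs.

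**The case against.** The strongest reply is that this is a preliminary analysis, done only if the data are sufficient, in a feasibility trial that tests no effectiveness hypothesis and whose primary outcomes are feasibility and acceptability. Interpolating utilities is routine, and a rule for apportioning costs is the kind of detail that an article leaves to a fuller plan. All of this stands as to severity, and the remark on utilities stands outright: the 26-week QALY places under 6% of its weight on week 32. It does not remove the mismatch. A fuller plan could supply a splitting rule, but only to work around a horizon already fixed.

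Three stronger readings are tempting and are not supported.

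- **A reader might infer that the 44 − 26 = 18 weeks after the horizon are thrown away.** The documents do not say so. The horizon is attached only to the cost-effectiveness estimate. The analyses of services used and their costs, of the QALY's ability to discriminate, and of missingness on the two utility measures carry no horizon. Even within the estimate, interpolation and apportionment draw on the 32-week data.
- **A reader might take it as given that economic measures are collected at 44 weeks.** That is likely from the wording on follow-up visits, but it is an assumption while the schedule figure is not shown.
- **A reader might add that the 16-week baseline recall matches no follow-up interval (20, 12 and 12 weeks).** No analysis stated in the article needs it to match.

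It is also fair to say that nothing in the documents makes 44 weeks the only acceptable base case. Ending at 20 or 32 weeks, or keeping 6 months with a stated splitting rule, would also resolve the inconsistency.

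**Conclusion.** The point holds, and it is minor. The stated horizon ends midway between two assessments. Under the recall period described, costs for weeks 20 to 26 can be obtained only by assuming how a 12-week total is spread, and an even split could be wrong by up to half of that total for a participant. The interpolation of utility is a lesser matter. Any 44-week economic data would contribute nothing to this one estimate, while remaining available for the other exploratory economic work.

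The mismatch rests only on figures in the article. The statement about 44-week data rests on the assumption that the economic measures are taken then; if they are not, less is lost but the horizon still meets no visit. The monetary size of any cost distortion cannot be given from the documents. No feasibility or acceptability conclusion depends on this.

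**What to change.** Replace the 6-month horizon with one that ends on an assessment. The preferred choice is 44 weeks: QALYs as the area under the curve through baseline, 20, 32 and 44 weeks, and costs as the sum of the three whole SUQ intervals (0–20, 20–32, 32–44). Report 20- and 32-week horizons as sensitivity analyses. If the schedule shows that economic measures are not taken at 44 weeks, use 32 weeks as the base case. If there is a reason to keep 6 months, state it, together with the rule for splitting the 32-week SUQ total and a range for the split.

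The cost is one sentence in the protocol or health economics plan. No new data are needed, nothing changes for participants, and 44 weeks stays under one year. The downside is more missing data at the later visit, which the shorter-horizon sensitivity analyses would help to show.

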#### Trial management and oversight arrangement

The trial is managed by a trial executive committee which consists of the chief investigator, co-investigators, the core project team, and other relevant parties that will meet quarterly. The management team will review study conduct including monitoring study progress, adherence to the protocol, and participant safeguarding. A programme management group comprising the chief investigator and core project team will meet weekly to oversee the day-to-day management of the programme. There is also a service user advisory group which will meet at least every 6 months and provide advice and feedback on a range of trial-related activities, e.g. reviewing study documents. The end of study will be reported to the Research Ethics Committee (REC) within the required timeframe if the study is terminated prematurely. Investigators will inform patients of any premature termination of the study and ensure that the appropriate follow-up is arranged for all involved. Following the end of the study, a summary report of the study will be provided to the REC within the required timeframe.

#### Data management

Participants will be allocated a study identity code for use on all study documents. The research team will create a confidential database of participant identifiable information and study identity code in order to allow the identification of participants enrolled in the study (e.g. for follow-up data collection). Access to study documents will be restricted to authorised persons. Participant consent forms will be filed in the corresponding site file and in participants’ medical notes. Baseline and follow-up data, which is anonymous data, will be stored in locked filing cabinets at GMMH. These data will be entered into an electronic database for analysis purposes by study team members blind to trial arm allocation. All computers are password protected and adhere to the secure storage policies of the NHS trust and University of Manchester.

Data quality checks will be performed on 10% of the data entered electrically from each time point at random by the statistical team. Data quality checks will review database entries with hard-copy questionnaire responses. Any discrepancies will be noted, corrected, and counted to obtain an error rate. Depending on the error rate, further checks will be performed.

#### Safety reporting

Adverse events (AEs) and serious adverse events (SAEs) will be monitored throughout the intervention delivery. Any adverse or serious adverse events identified as likely to be caused by the intervention during the study recruitment or intervention phase will be recorded at the study site using an AE/SAE record form which will be completed by the participants’ health professional delivering treatment. AEs and SAEs will be reported to the research team and reviewed for seriousness and causality by a designated study investigator who is not blind to treatment allocation. Any that are deemed SAEs, and are related to the intervention, will be reported to the ethics committee, the programme executive committee, and the sponsor’s Research and Innovation Manager within 7 days of the event. AEs and SAEs will be reviewed on a quarterly basis at executive committee meetings.

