## Trial conditions

### Group metacognitive therapy (group-MCT)

Group-MCT will include 8 weekly sessions of group-based MCT. Sessions will last approximately 90 min and be guided by a treatment manual to maximise treatment adherence and fidelity. Groups may range from a minimum of 3 participants to a maximum of 10 participants, with the same therapists at each site delivering all eight sessions.

Group-MCT aims to help participants develop knowledge that can facilitate control of worry, repetitive negative thinking, and attention and to modify the metacognitive beliefs that maintain unhelpful thinking patterns [16].

Eight main treatment techniques will be used across sessions: (1) formulation, (2) socialisation, (3) the Spatial Attentional Control Exercise (SpACE), (4) detached mindfulness, (5) worry and rumination postponement, (6) modifying metacognitive beliefs about worry and rumination, (7) a ‘helpful behaviours prescription’, and (8) individual treatment summaries. Sessions include group discussions, experiential learning, and homework tasks that participants are asked to complete between sessions.

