### Treatment as usual (TAU)

TAU will consist of routine care delivered within CAMHS. Therapies delivered include but are not limited to cognitive behavioural-based therapies (CBT), behavioural activation, exposure therapy, Eye Movement Desensitization and Reprocessing (EMDR), and family therapy delivered on a one-to-one or group basis. Participants normally receive up to 12 (1-h) sessions of TAU.

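### The safety section makes attribution to the intervention a condition for recording an adverse event and limits recording to an undefined phase, so event counts would reflect attribution and could not be compared between arms

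*Protocol article*

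**What the plan says.** The Safety reporting section of the protocol article has four steps.

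1. Monitoring, with no causal condition: "Adverse events (AEs) and serious adverse events (SAEs) will be monitored throughout the intervention delivery".
2. Recording, with a causal condition and a time limit: "Any adverse or serious adverse events identified as likely to be caused by the intervention during the study recruitment or intervention phase will be recorded". This is done on a form "which will be completed by the participants’ health professional delivering treatment".
3. Review: reported events are "reviewed for seriousness and causality by a designated study investigator who is not blind to treatment allocation".
4. Escalation within 7 days, limited to serious events that are related to the intervention.

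The Design section fixes what the word intervention means; the trial is described as "comparing group-based MCT (intervention) versus usual treatment (control)". On duration, the group-MCT section says "Group-MCT will include 8 weekly sessions of group-based MCT", the TAU section says "Participants normally receive up to 12 (1-h) sessions of TAU", and Data collection says "Participants’ time involvement in the study is 44 weeks", with assessments at baseline and at 20, 32 and 44 weeks. No section describes recording of adverse events at the 20-, 32- or 44-week assessments.

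**The concern.** Limiting expedited reporting to related serious events is ordinary practice. Here the same test is also applied one step earlier, to what goes on the form. An event that nobody linked to group-MCT at the time leaves no record, and no analysis plan can restore it.

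The article says there has been no randomised trial of MCT in children and young people, and this study is meant to inform a definitive one. Whether harms can be collected evenly in both arms, and roughly how often they occur, belongs to that decision. TAU is itself active therapy (the TAU section names CBT, exposure and EMDR among others), so the comparison is a fair question. Under the rule as written, a low count in the group-MCT arm or an empty TAU column could come from the recording condition alone, and a reader of the results could not tell.

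**Working it through.** The documents give no event rate and no precision target for harms, so there is no figure of the plan's own to reproduce. The check is textual, with arithmetic to show size.

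**Step 1: order of the filters.** Recording requires attribution to the intervention. Causality review comes after recording. The reviewed set is therefore a subset of events already attributed. The review can move an event from related to unrelated, but it cannot move one from unrecorded to recorded. The neighbouring sentences sit badly with this. Monitoring is unconditional, and both a separate causality review and a relatedness test at escalation would be largely redundant if only attributed events ever reached them. Either the recording sentence or the others must give way.

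**Step 2: which arm can qualify.** With group-MCT as the intervention and usual treatment as the control, an event in a TAU participant does not satisfy the recording condition as worded.

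**Step 3: what the counts would show.** Inputs: 50 per arm (Sample size calculation); an event rate of 20% in both arms (assumed); 10% to 50% of group-MCT events attributed to group-MCT (assumed).
- True events per arm: 50 × 0.20 = 10.
- Recorded in group-MCT: 10 × 0.10 = 1 to 10 × 0.50 = 5.
- Recorded in TAU on the literal wording: 0.

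With identical true risk, the table would read 1–5 against 0. At assumed rates of 10% and 30%, the recorded group-MCT counts would be 0.5–2.5 and 1.5–7.5, where all-cause recording would expect 5 and 15 per arm.

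The same problem affects a zero count. The exact one-sided 95% upper limit for 0/50 is 1 − 0.05^(1/50) = 5.8%. A reader could compute that limit, but it would bound the rate of attributed and recorded events, not the rate of events.

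**Step 4: how much follow-up is covered.** Participation is 44 weeks, and the intervention phase is not defined. Three readings of where it ends for a participant, counted from randomisation:

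| Phase ends at | Covered | Uncovered |
|---|---|---|
| week 8 (eight weekly sessions, started at once) | 8/44 = 18% | 36/44 = 82% |
| week 12 (TAU, if its 12 sessions are weekly and start at once; spacing not stated) | 12/44 = 27% | 32/44 = 73% |
| week 20 (first follow-up) | 20/44 = 45% | 24/44 = 55% |

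If the phase is a calendar period for the whole trial, early participants would be covered for longer than the table shows.

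**Step 5: what all-cause recording would give.** The 95% half-width for a difference in proportions with 50 per arm is 1.96 × √(2p(1−p)/50). For assumed common rates of 5%, 10%, 20% and 30% this is 8.5, 11.8, 15.7 and 18.0 percentage points. That is enough for description by arm, not for a safety test.

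**The case against.** The strongest reply is that this is a short paragraph in a condensed article about a feasibility trial that tests no hypotheses of effectiveness, and that its other sentences point to wider capture. Definitions, windows and TAU procedures may sit in the full protocol. That stands for anything the article merely leaves out. It does not answer a restrictive condition that the article states.

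Four stronger readings are tempting, and the documents do not support them.

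- **The therapist decides causality.** The recording sentence uses a passive verb. The article says who completes the form, not who attributes cause. The therapist as judge is an inference, although no one else is named at that step.
- **Half the sample has no recordable events.** This follows from the literal wording and the label in Design. But a professional delivering treatment exists in the TAU arm too, and a reviewer aware of allocation is compatible with events arriving from both arms. In practice TAU events may be recorded; the text does not provide for it.
- **82% of follow-up is unobserved.** That is the extreme case. Groups need at least three participants, so therapy will often start later than randomisation, and the sentence also covers the recruitment phase.
- **Late harm cannot be seen and no safety information can be compared between arms.** RCADS-25 and MFQ can show worsening, the service-use questionnaire asks about contacts since the last assessment, and drop-out reasons are recorded where possible. These run in both arms. They are indirect: none records an event as such or assesses its seriousness or relatedness.

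**Conclusion.** The point holds as a defect in the recording rule. As worded, adverse-event counts depend on attribution to group-MCT, TAU events do not meet the condition, and the later review cannot repair what was not recorded. The counts therefore could not be compared between arms. The rule also conflicts with the other sentences of the same section, and these must be reconciled.

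Post-treatment events are recorded only if the undefined intervention phase reaches them: about 55% of the 44 weeks is uncovered if it ends at week 20, and up to 82% if it equals eight sessions begun at once. The 1–5 against 0 illustration rests on assumed event and attribution rates. What is lost is descriptive harm data by arm and evidence that such data can be collected, not a powered safety comparison.

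**What to change.** Rewrite the Safety reporting section so that its sentences agree:

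- Remove attribution to the intervention as a condition for recording.
- Record adverse events in both arms from randomisation to week 44, whatever the suspected cause. At minimum this means all serious events plus a prespecified list such as self-harm, crisis contact and marked deterioration.
- Ask the same event question in both arms at the existing 20-, 32- and 44-week contacts.
- Let the designated investigator judge seriousness and relatedness after recording.
- Keep expedited reporting for related serious events, as now.
- Tabulate events descriptively by arm.

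No extra visits are needed, but the change is not free. There will be more forms. Research assistants are to stay blind until all outcomes are collected, so the question must be worded, or the answers routed, so that allocation is not disclosed. Because follow-up measures may be returned by post, a process is also needed for reviewing events disclosed that way. The shorter list of serious and prespecified events keeps this burden down if recording every minor event to week 44 is thought too much.
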